#### Baseline Characteristics

Initially, descriptive statistics for the sample characteristics will be done for the intervention group and the wait-list control group to assess the distribution of important predictors of the outcome between both groups at baseline.

#### Primary Outcome Measure: HIV Risk Perception Score

First, we will use bivariate analysis to calculate the mean between baselines and follow-up. Next, to estimate the difference between the 2 groups, we will calculate the difference between the mean change of the intervention group and the mean change of the wait-list control group using two-sample paired *t* test. We will not perform interim analysis.

Secondly, in the case that, even after randomization, we observe some baseline differences, we will use multiple linear regression to adjust for those differences; where the outcome will be the follow-up score and the independent variables will be the intervention group, baseline scores, age, gender, marital status, level of education employment status, current monthly income, and number of times players played SwaziYolo. We will present our results in standardized regression coefficients for the intervention effect on the outcome variable as previously done for this type of hypothesis [25].

Although great effort will be put to minimize attrition, it is common for eHealth trials to typically have substantial attrition [26]. For this reason, our primary outcome analysis will prioritize analysis of the subjects who adhered to their group assignment and were sufficiently exposed to the intervention. Therefore, both pre-protocol analysis (as treated analysis) as well as intention to treat analysis will be done and both results will be reported. The approach of conducting both “intention to treat analysis” together with “as treated analysis” has been observed in literature for example, Weinstein and colleagues [33] followed this approach in their randomized trial comparing surgical versus nonoperative treatment for lumbar disk herniation.

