**Methods:**

This is a two-arm randomized intervention trial. We will recruit 380 participants who meet the following eligibility criteria: 18-29 years of age, own a smartphone running an Android-based operating system, have the WhatsApp messaging app, live in Swaziland, and can adequately grant informed consent. Participants will be allocated into a smartphone interactive, educational story game, and a wait-list control group in a 1:1 allocation ratio. Subsequently, a self-administered Web-based questionnaire will be issued at baseline and after 4 weeks of exposure to the game. We hypothesize that the change in HIV risk perception between pre- and post-intervention assessment is greater in the intervention group compared with the change in the control group. Our primary hypothesis is based on the assumption that increased perceived risk of HIV provides cues to engage in protective behavior. Our primary outcome measure is HIV risk perceived mean change between pre- and post-intervention compared with the mean change in the wait-list control group at 4-weeks post-intervention. We will use standardized regression coefficients to calculate the effect of the intervention on our primary outcome with *P* values. We will conduct both intention to treat and as treated analysis.

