### Sample Size Calculation

The trial will be powered on the primary outcome measure and based on comparison of the change in HIV risk perception score from pre- to post-intervention assessment in the intervention group at 4 weeks. A study conducted in Uganda estimated mean HIV risk perception of M=3.27, SD *=* 1.03, therefore, we used this estimation as our baseline mean and SD to calculate our effect size [21]. Assuming a moderate effect size of 0.477 (identified by Chu et al [22]), alpha (two-tailed)=0.05, beta=0.20, with 1:1 allocation ratio between both groups, and a SD of the outcome in the population of 1.03, the total sample required to sufficiently power the study would be 146 (73 for each group). Moreover, assuming a 30% loss to follow-up rate [15], we then inflated the sample by 30% to yield a sample of 190. After that, we considered gender differences and once more inflated the sample by a factor of 2 to give a final sample size of 380. Finally, to ensure a balance between males and females in both groups we will recruit 190 females and 190 males. The sample size was calculated using Web-based sample size calculation software [23,24].

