### Randomization

Upon confirmation of participants’ trial registration, participants will be assigned another unique code called “game unlock code,” which will be used for randomization using secure, remote, Web-based computer software within 24 hours of recruitment. As stated in the research design, participants will be randomized into 2 groups; the intervention group and the wait-list control group in a 1:1 ratio. The data analysis team will be blinded in this study, however, participants will not be blinded.

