#### Primary Outcome Measure

Adding one or more comparison groups to a pre- and post-intervention assessment will result in a stronger intervention design than having a single intervention group to a pre- and post-intervention assessment [26]. Therefore, the primary intervention outcome will be the change in HIV risk perception score from pre- to post-intervention assessment in the intervention group compared with the change in the wait-list control group. High perception is considered to be the first stage toward behavioral change and has been associated with HIV protective HIV behavior [27,28]. HIV risk perception using the PRHS will be used to measure the primary outcome at baseline and at 4-weeks follow-up.

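### The primary between-arm test is named as paired although the arms are independent, and the baseline-adjusted model depends on an undefined trigger; one unconditional ANCOVA should lead

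*Protocol article*

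**What the plan says.** The section Primary Outcome Measure defines the outcome as "the change in HIV risk perception score from pre- to post-intervention assessment in the intervention group compared with the change in the wait-list control group". Randomization describes two parallel groups: "participants will be randomized into 2 groups; the intervention group and the wait-list control group in a 1:1 ratio". No matching is mentioned anywhere.

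Under Data Management and Statistical Analysis, the section Primary Outcome Measure: HIV Risk Perception Score sets the mean change in the intervention arm against "the mean change of the wait-list control group using two-sample paired" *t* test. It then adds a second analysis: "in the case that, even after randomization, we observe some baseline differences, we will use multiple linear regression to adjust for those differences". That model is an ANCOVA in form, "where the outcome will be the follow-up score and the independent variables will be the intervention group, baseline scores", followed by demographic variables and "number of times players played SwaziYolo". Its arm effect is to be shown as a standardised coefficient.

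The abstract's Methods paragraph gives the regression with no condition: "We will use standardized regression coefficients to calculate the effect of the intervention on our primary outcome". Current Status, under Results, lists mean differences with 95% confidence intervals as well as standardised coefficients.

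**The concern.** Three things are unsettled in the text that decides hypothesis 1.

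- **The test name.** A paired test needs a partner in the other arm for each participant. None is defined, and the test cannot be computed if the arms finish with different numbers, which is likely when 30% loss is assumed.
- **The role of the regression.** It runs only if baseline differences are seen. No variable, threshold or criterion says what counts as a difference, and nothing says which result is primary when both exist. The abstract and the analysis section disagree on whether the regression is conditional at all.
- **The covariates.** The play count arises after randomisation. Description of the Intervention says that wait-list participants do not play until the post-intervention assessment, so the count is zero by design in that arm. With it in the model, the arm coefficient no longer estimates the randomised effect. It becomes a contrast between controls and a hypothetical intervention participant with zero plays, and the play-count term absorbs the rest of the effect.

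At stake is whether the trial has one defined primary result, fixed before any data are seen.

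**Working it through.** **Inputs.** Sample Size Calculation gives a difference of 0.477, SD 1.03, 30% loss and a final total of 380, with "alpha (two-tailed)=0.05, beta=0.20, with 1:1 allocation ratio between both groups". The SD is that of a score. The article gives no SD of change and no pre-post correlation rho, so rho is assumed below and a range is shown.

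**1. Reproduce the plan's figure.** For two independent means:

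n per arm = 2 × (1.960 + 0.842)² × 1.03² / 0.477² = 73.19, against 73 stated (74 if rounded up).

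A paired or one-sample *t* calculation needs 38.6 pairs with 0.477/1.03 as the standardised effect, or 36.5 with 0.477 itself, that is 39 or 37 pairs. The plan's own number therefore comes from an independent comparison.

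**2. Change score against ANCOVA.**

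- SD of change = 1.03 × √(2(1 − rho))
- ANCOVA residual SD = 1.03 × √(1 − rho²)
- Variance ratio = (1 − rho²) / (2(1 − rho)) = (1 + rho)/2

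Expected completers: 380 × 0.7 = 266, or 133 per arm. Power (normal approximation) = Φ(0.477 / (SD × √(2/n)) − 1.96):

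| rho (assumed) | Variance ratio | Change score, n = 73 | ANCOVA, n = 73 | Change score, n = 133 | ANCOVA, n = 133 |
|---|---|---|---|---|---|
| 0 | 0.50 | 51% | 80% | 76% | 97% |
| 0.1 | 0.55 | 55% | 80% | 80% | 97% |
| 0.3 | 0.65 | 66% | 84% | 89% | 98% |
| 0.5 | 0.75 | 80% | 90% | 96% | 99% |
| 0.7 | 0.85 | 95% | 98% | 99.8% | >99.9% |

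**3. The conditional rule.** Simulation at 73 per arm, with two assumptions that the article does not state: the trigger is P < 0.05 on the baseline score, and the regression leads when triggered.

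| Type I error | rho 0.3 | rho 0.5 | rho 0.7 |
|---|---|---|---|
| Rule followed strictly | 3.6% | 4.5% | 4.5% |
| Both run, either may be claimed | 7.7% | 7.6% | 6.8% |
| Change score, only trials with imbalance | 23% | 18% | 13% |
| ANCOVA, only trials with imbalance | 5.5% | 5.6% | 5.2% |

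The third row arises because the between-arm difference in change is correlated with the baseline difference by −√((1 − rho)/2), which is −0.59, −0.50 and −0.39. A chance baseline difference therefore carries into the change-score result. ANCOVA removes it.

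**4. Arbitrary pairing.** In the same simulation, pairing equal arms at random kept type I error at about 5% (4.7% to 5.2%). The fault is an undefined test; no inflation of alpha was shown.

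**5. Reporting scale.** With equal arms, a 0.477-point effect has a standardised coefficient of 0.477 × 0.5 / √(1.03² + 0.477²/4) = 0.23. That is not on the scale on which the trial was sized.

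**The case against.** The best reply is that the intended contrast is plain. The sentence itself asks for the difference between the two arms' mean changes, and *paired* most naturally refers to each person's pre-post pair. A two-sample *t* test on those changes is valid, and the sample size fits it. The comparison is also run unconditionally, with the regression added second. Both change-score and ANCOVA estimates are unbiased under randomisation. These points stand, and they limit what may be inferred.

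- **That hypothesis 1 has no valid test.** A reader might infer this, but the stated contrast and the sample size point to a naming slip.
- **That the *t* test is swapped for another model after the data are seen, or that alpha is inflated.** The text adds the regression and does not replace the *t* test. Followed strictly, the rule gave at most 4.5% type I error. The 7% to 8% figure needs the further assumption that either result may be claimed.
- **That the trial is underpowered unless rho is about 0.5.** That holds at 73 per arm, which is the number before inflation. The planned comparison expects about 133 per arm. The smaller figure would matter for separate analyses by gender, but the article names no such test.
- **That the effect will appear only as a standardised coefficient.** Current Status already plans mean differences with confidence intervals, though it does not say whether they are adjusted.

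The reply does not cover the missing trigger criterion, the silence on which result leads, the disagreement with the abstract, or the play-count covariate.

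**Conclusion.** The point holds in a limited form. The named test is wrong as written for two independent arms, probably through a slip. The baseline-adjusted model has an undefined trigger and no stated rank, and the abstract and the analysis section conflict on it. The listed regression cannot simply be promoted to primary, because the play count would absorb the arm effect.

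The gain from one unconditional ANCOVA is a single defined result and better precision: variance 0.65, 0.75 or 0.85 of the change-score variance at rho 0.3, 0.5 or 0.7. It also protects against chance baseline imbalance, after which the change-score test rejected a true null in 13% to 23% of simulated trials. These sizes rest on assumed values of rho, equal SDs at both times, and the assumed trigger. Change-score power at 133 per arm is about 80% at rho 0.1 and higher above that, so adequacy of the sample is not in question here.

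**What to change.** - Name one primary analysis, run regardless of observed imbalance: linear regression (ANCOVA) of the 4-week PRHS score on arm, baseline PRHS and gender. Any further covariates should be pre-randomisation and fixed in advance.
- Explicitly delete the number of game plays from the covariates.
- Report the adjusted mean difference in PRHS points with 95% CI and P value as the lead estimate. Keep the standardised coefficient as supplementary.
- Keep an independent-samples *t* test on change scores as a sensitivity analysis, and delete the word *paired*.
- Remove the clause that makes the regression depend on observed baseline differences, and align the abstract with the analysis section.

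The cost is wording. No extra data or participants are needed, the baseline score is already collected, and Current Status describes the study as not yet started, so the choice can be fixed before any outcome is seen.

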**Sexual reproductive history**			
	Condom use in the last sex	X^a^	X
	Number of sexual partners	X	X

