**Steady sexual partner’s history**			
	Has current sexual partner ever tested for HIV?	X	X
	Knowledge of current partner’s HIV status	X	X

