**Demographics**			
	Age	X	
	Level of education	X	
	Employment status	X	
	Income level	X	
	Marital status	X	
	Ever tested for HIV	X	X

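### The adjusted primary model is meant to correct observed baseline differences, but its fixed covariate list holds no sexual-risk or HIV-testing variable, so part of an imbalance in these can remain

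*Protocol article*

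**What the plan says.** The Baseline Characteristics section of the protocol article compares the arms "to assess the distribution of important predictors of the outcome between both groups at baseline". The section on the primary outcome analysis then provides that, should the arms differ at baseline despite randomisation, "we will use multiple linear regression to adjust for those differences". The outcome of that regression is the follow-up score. Besides study arm, the independent variables are "baseline scores, age, gender, marital status, level of education employment status, current monthly income, and number of times players played SwaziYolo". The list is closed: apart from the baseline score and the play count, it has age, gender and four sociodemographic items (marital status, education, employment, income).

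Table 1 shows what else is recorded at baseline. The sexual history block has condom use at last sex and "Number of sexual partners". The steady-partner block has "Has current sexual partner ever tested for HIV" and knowledge of the partner's status. The demographics block has "Ever tested for HIV". None of these five items is in the model.

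The same analysis section gives priority to participants who kept to their allocation and had enough exposure to the game. Intention to treat is reported as well.

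**The concern.** The rule has a stated job: to remove differences seen between the arms in predictors of the outcome. A fixed list can do that only for the variables on it. If the arms differ on number of partners, the model as written adjusts for income and employment and leaves number of partners out.

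The omitted items are not remote from the outcome. Hypothesis 2 looks at change in risk perception among people reporting high-risk behaviour. The Secondary Outcome Measures section defines a subgroup by condom use at last sex. The Introduction says national HIV testing guidelines include a risk assessment meant to raise a person's own sense of risk.

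At stake is an estimate labelled as adjusted that still carries part of a visible imbalance, together with a little precision that data already collected could supply. This point concerns which baseline variables are on the list. It does not depend on the imbalance trigger or on the play-count term, which are separate questions about the same sentence.

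**Working it through.** **Plan's own figure.** Sample Size Calculation: difference 0.477, SD 1.03, two-sided alpha 0.05, power 0.80. Per arm, 2 × (1.960 + 0.842)² × (1.03/0.477)² = 73.2. That matches the stated 73 per group (146 in total) up to rounding. The planned effect is therefore 0.477/1.03 = 0.463 SD.

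**Numbers analysed.** 380 enrolled; with the plan's 30% loss, 380 × 0.70 = 266, or 133 per arm.

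**Size of a chance imbalance.** For a standardised covariate X the arm difference has standard error 2/√N: 0.103 SD at N = 380 and 0.123 SD at N = 266. At the 1.96 limit the difference is 0.201 SD and 0.240 SD.

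**What remains after adjusting for the baseline score.** Let r1 be the correlation of X with the baseline score, r2 of X with the follow-up score, and r3 of baseline with follow-up. With no adjustment, an imbalance d moves the estimate by r2 × d. With the baseline score in the model the expected shift is (r2 − r1 × r3) × d. The documents give no correlations, so these are assumptions. N = 266, d = 0.240:

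| r1 | r2 | r3 | No adjustment (SD) | Baseline score in model (SD) |
|---|---|---|---|---|
| 0.5 | 0.3 | 0.6 | 0.072 | 0.000 |
| 0.3 | 0.2 | 0.6 | 0.048 | 0.005 |
| 0.3 | 0.3 | 0.6 | 0.072 | 0.029 |
| 0.3 | 0.3 | 0.5 | 0.072 | 0.036 |
| 0.4 | 0.4 | 0.6 | 0.096 | 0.038 |
| 0.2 | 0.3 | 0.6 | 0.072 | 0.043 |

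The largest residual is 0.043/0.463 = 9% of the planned effect. At N = 380 the residuals run from 0.000 to 0.036 SD.

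**Binary variable.** Assume 50% prevalence and an effect on follow-up, beyond the baseline score, of 0.15 to 0.45 SD. Among simulated trials with 133 per arm in which the imbalance reaches the 5% level, it averages about 14 percentage points. The shift is then 0.14 × 0.15 = 0.021 SD to 0.14 × 0.45 = 0.063 SD, or 5% to 14% of 0.463. Simulation (baseline coefficient 0.5) gave 0.023, 0.040 and 0.063 SD for effects of 0.15, 0.30 and 0.45 SD. The false-positive rate in those selected trials was roughly 6% to 8%.

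**Over all randomisations.** 20,000 simulated trials at N = 266 (correlations 0.3, 0.3, 0.6; true effect set to 0.477 SD) gave a mean estimate of 0.477 with X omitted and 0.477 with X included. The empirical SDs were 0.098 and 0.097. In the trials with X imbalanced beyond 1.96 SE towards the intervention arm, the means were 0.503 and 0.468. In the binary setting, including the variable lowers the variance of the estimate by about 0.4% to 6%.

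**Adherent and exposed set.** Illustration with assumed rates: 70% of lower-risk and 50% of higher-risk intervention participants count as sufficiently exposed, all controls qualify, and half of each arm is higher-risk. The higher-risk share in the intervention arm becomes 0.25/(0.25 + 0.35) = 42%, against 50% in controls. That 8-point gap moves the estimate by about 0.083 × 0.15 = 0.01 SD to 0.083 × 0.45 = 0.04 SD. It does not shrink with sample size, because selection produces it.

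**The case against.** The strongest reply is that the baseline risk-perception score is already in the model. The scale covers perceived chance of infection, worry, vulnerability and salience, so it takes up whatever part of a risk-behaviour imbalance acts through baseline perception. This stands, and the table shows that the remainder is usually the smaller part.

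Second, under intention to treat a chance imbalance is covered by the standard error, and a prespecified list need not contain every measured variable. This also stands.

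Third, hypothesis 2 and the condom-use subgroup concern where the effect may be larger. They do not show that these items predict the follow-up score given the baseline score. The Discussion notes that people with risky behaviour often do not see themselves at high risk, and where it links perception to testing or condom use, the direction is from perception to behaviour. So the prognostic value of these items is plausible but not established by the document.

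Fourth, the items are not clean baseline data. Under Baseline Data Collection the questionnaire follows randomisation, and participants are not blinded, so answers may reflect allocation. That is true, but the baseline score, already in the model, shares the weakness.

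What survives is the mismatch between the stated purpose and the list, and the prioritised analysis, to which the chance-imbalance argument does not apply.

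**Conclusion.** The point holds in a limited form. The regression is offered to correct observed differences in predictors of the outcome, and its closed list cannot do so when the difference lies in sexual risk or testing history. Conditional on a marked imbalance, the residual shift is about 0 to 0.06 SD, at most about 14% of the planned 0.463 SD. That range rests on assumed correlations and partial effects.

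A reader might infer that the whole imbalance stays in the estimate, or that the intention-to-treat result is biased. The documents support neither: the baseline score is a covariate, and the estimate is unbiased over randomisation. Nor does it follow that every Table 1 item must be modelled.

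The omission weighs more in the adherent and sufficiently exposed analysis, which the plan puts first. Membership of that set is decided after randomisation and may depend on risk behaviour, so differences there need not be chance. How large they would be cannot be read from the document; the 0.01 to 0.04 SD above is an illustration.

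**What to change.** In the primary outcome analysis section, add to the fixed covariate list a short set of baseline items already collected: number of sexual partners, condom use at last sex, and ever tested for HIV. Give participants to whom an item does not apply their own category, so that nobody drops out of the model, and check the coding against the questionnaire in Multimedia Appendix 2. State that the same set is used in the intention-to-treat and the adherent/exposed analyses.

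The cost is one sentence and a few degrees of freedom out of about 266 completers, with no new data. The limitation is that the items are self-reported after unblinded allocation. The report should say so, for these items and for the baseline score.

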## Results

### Current Status

The status of the study is in preinitiation stage. Results are expected in February 2017. We will present results as percentages, observed means with 95% confidence intervals, mean difference and 95% confidence intervals, standardized regression coefficients, and *P* values. All analysis will be performed using SPSS for Windows.

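### The adjusted intervention effect is planned only as a standardized coefficient for arm, which is not in score units and varies with the arm split; report the adjusted PRHS difference with its 95% CI instead

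*Protocol article*

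**What the plan says.** The reporting scale is named in three places in the protocol article.

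- Abstract, Methods: "We will use standardized regression coefficients to calculate the effect of the intervention on our primary outcome with" P values. This is the only effect measure the abstract names for the analysis.
- Primary Outcome Measure: HIV Risk Perception Score (under Data Management and Statistical Analysis): "We will present our results in standardized regression coefficients for the intervention effect on the outcome variable".
- Results, Current Status: the formats listed are percentages, then "observed means with 95% confidence intervals, mean difference and 95% confidence intervals, standardized regression coefficients, and" P values.

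The regression comes second. The first analysis compares the mean change in the two groups. The regression follows if "we observe some baseline differences, we will use multiple linear regression to adjust for those differences". Its outcome is the follow-up score. Its predictors are arm, baseline score, sociodemographic variables and the number of times the game was played.

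The same section plans both an intention-to-treat analysis and an as-treated (per-protocol) analysis, and will report both. It gives priority to participants who kept to their assignment and had enough exposure to the game.

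The primary outcome, as defined under Measurement Instrument, is the difference between groups in change of score. The trial was sized with the words "Assuming a moderate effect size of 0.477" and "a SD of the outcome in the population of 1.03".

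**The concern.** A standardized coefficient suits a continuous predictor, where one SD of the predictor means something. For a two-level arm variable, the SD of the predictor depends only on how the analysed participants divide between arms. Multiplying the effect by that SD takes it off the score scale and ties it to the split.

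Three consequences follow.

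- When the regression is needed, the reader gets a number that is neither a difference in PRHS points nor a standardized mean difference, and it stands in the same article as a sizing effect of 0.477.
- The exposure requirement can remove participants from the intervention arm only, because wait-list controls are not to play before the post-intervention assessment (Description of the Intervention). The as-treated split may then differ from the intention-to-treat split, and a small part of any gap between the two coefficients would come from scale alone.
- No confidence interval is attached to the adjusted effect.

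**Working it through.** **Inputs.** Sample Size Calculation gives a difference of 0.477, SD 1.03, two-sided alpha 0.05, power 0.80, 1:1 allocation and 73 per group. The plan gives no as-treated split, so the intervention share p is varied as an assumption.

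**1. Reproduce the plan's figure.** With 0.477 as a raw difference,

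n per arm = 2 × [1.03 × (1.960 + 0.842) / 0.477]² = 73.19,

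which matches the stated 73. With 0.477 as already in SD units, the same formula gives 68.99, i.e. 69 (70 with the t distribution), which does not match. In effect the trial was sized on a raw difference b = 0.477, so d = 0.477 / 1.03 = 0.463.

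**2. Standardized coefficient for arm.** Any two-level coding gives the same value up to sign:

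beta = b × √(p(1−p)) / SD(Y), with SD(Y)² = 1.03² + b² p(1−p).

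At p = 0.5: 0.477 × 0.5 = 0.2385, and SD(Y) = √(1.0609 + 0.0569) = 1.057. So beta = 0.2385 / 1.057 = 0.226, which is 48.7% of d. If 0.477 is taken as the standardized difference instead, beta = 0.232, or 48.6% of it.

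**3. Same true effect, different splits.**

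| Intervention : control | b (points) | beta | Change from 1:1 |
|---|---|---|---|
| 50:50 | 0.477 | 0.226 | – |
| 40:60 | 0.477 | 0.221 | −2% |
| 1:2 | 0.477 | 0.213 | −5% |
| 30:70 | 0.477 | 0.208 | −8% |
| 20:80 | 0.477 | 0.182 | −19% |

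A simulated regression with a baseline covariate (assumed pre-post correlation 0.5) gave beta of 0.226, 0.214 and 0.183 at shares of 0.50, 0.333 and 0.20. The raw coefficient stayed between 0.477 and 0.479.

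**4. Converting back.** d = beta / √(p(1−p)(1−beta²)). At p = 0.5 this is 0.2256 / (0.5 × √(1 − 0.0509)) = 0.463, and it returns 0.463 at every split above.

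**5. The play count.** By design controls have zero plays. With the play count in the model, the arm coefficient compares controls with an intervention participant who never played. That holds for the standardized and the unstandardized coefficient alike, and neither is then the adjusted mean difference. The calculations in steps 2 to 4 describe a model without this covariate.

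**The case against.** The case for leaving the plan alone has several sound parts.

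- The first analysis already gives the difference in mean change, which matches the primary outcome, and the regression runs only if baseline differences appear. Both points stand.
- The Current Status section promises a mean difference with 95% CI, which does not depend on the split. This stands for the unadjusted comparison. The text does not say that this difference is adjusted, so it does not clearly cover the regression.
- A standardized coefficient is a correlation-type measure. It differs from a standardized mean difference by definition, and no section proposes setting it against 0.477. This stands: 0.23 is not a wrong number.
- The scale shift is small beside sampling error. With 133 per arm (190 × 0.7), the unadjusted standard error of beta is about 1.03 × √(2/133) × 0.5 / 1.03 = 0.061. The shift at 1:2 is 0.2256 − 0.2133 = 0.012, a fifth of that. This also stands.
- The SD of 1.03 comes from a Ugandan study whose source is cited among users of single likelihood questions, so PRHS points need not match the sizing figures. This is true, and it makes the point-scale numbers illustrative. The dependence of beta on the split does not rest on it.

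A reader might infer that the intention-to-treat and as-treated results cannot be compared at all, or that the trial would report half its true effect. The documents support neither. Mean differences are also planned, the coefficient converts back from the arm sizes, and the distortion is modest unless the split is extreme.

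**Conclusion.** The point holds as a reporting weakness of modest size. The plan gives the adjusted intervention effect only as a standardized coefficient for arm. That coefficient would be about 0.23 at 1:1 if the planned effect is achieved, and 2% to 8% lower for splits between 40:60 and 30:70. A split-free adjusted estimate in score points, with a confidence interval, is not clearly promised.

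This rests on three assumptions: that standardized means fully standardized, which is the usual sense but is not spelled out; that the as-treated set is unbalanced, which the exposure filter makes plausible but the plan does not quantify; and that the sizing figures are used as the true effect. The effect on the intention-to-treat versus as-treated comparison is nil if the two splits are equal. The change of scale does not alter P values or the unadjusted comparison of mean changes.

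**What to change.** In the Abstract (Methods), in Primary Outcome Measure: HIV Risk Perception Score, and in Current Status:

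- Name the unstandardized arm coefficient, i.e. the adjusted difference in PRHS score at 4 weeks, as the reported effect from the regression, with 95% CI and P value, for both the intention-to-treat and the as-treated set.
- Take it from a model with baseline covariates only. Leave out the play count, which arises after randomization.
- If a scale-free value is wanted, divide the coefficient and its limits by one pooled baseline SD of the PRHS score, the same for both sets.
- Keep the standardized coefficient, if at all, as a supplement for comparison with the cited precedent.

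The cost is wording. The plan states "All analysis will be performed using SPSS for Windows", and SPSS prints the unstandardized coefficient and can print its interval from the same model. Sample size and data collection are untouched. The one downside of the new scale is less direct comparability with the cited precedent. Removing the play count does change the fitted model, and so its arm coefficient and P value; that is intended, because only then is the coefficient an adjusted mean difference.
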